### Sample size

The minimum clinically important difference (MCID) for the primary outcome measure (DRI) is assumed to be eight points.^13^ The DRI is a 12-item, patient-reported, functional outcome questionnaire that is transformed to a 100 point scale, where 0 represents normal function and 100 complete disability. At an individual patient level, a difference of eight points represents the ability to climb stairs or run with ‘some difficulty’ versus with ‘great difficulty’. At a population level, eight points represents the difference between a ‘healthy patient’ and a ‘patient with a minor disability’.

In table 1, the bold figure of 412 patients represents a conservative scenario, based on a SD of 25 and 90% power to detect the selected MCID. However, a sample size of 308 patients would still provide 80% power. Allowing a margin of 10% loss during follow-up, including the small number of patients who die in the first year following their injury, this gives a figure of *460* patients in total. Therefore, 230 patients who consent to each group will provide 90% power to detect a difference of eight points in DRI at 12 months at the 5% level.

**Table 1 BMJOPEN2015009087TB1:** Sample size for varying power and SD

SD	Power	
	80%	90%
15	112	150
20	198	264
25	308	**412**

The sample size used in the trial is shown in bold.

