#### Randomisation

The allocation sequence will be generated by an independent randomisation centre—York CTU. Randomisation will be on a 1:1 basis, stratified by trial centre and Gustilo and Anderson grade—2, 3, or 3 with vascular injury requiring surgical repair. Eligibility for the trial is based on a wound of grade 2 or above, which will be established definitively at the end of the initial surgical debridement in the operating theatre as per routine clinical practice. Therefore, participants will be assigned to their treatment allocation at the end of the initial surgery, but before the wound dressing is applied. All modern operating theatres include a computer with web-access; so a secure, 24 h, web-based randomisation system will be used to generate the treatment allocation intraoperatively.

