### Main RCT

Standard statistical summaries (eg, medians and ranges or means and variances dependent on the distribution of the outcome) and graphical plots showing correlations will be presented for the primary outcome measure and all secondary outcome measures. Baseline data will be summarised to check comparability between treatment arms, and to highlight any characteristic differences between those individuals in the study, those ineligible and those eligible, but withholding consent.

The main analysis will investigate differences in the primary outcome measure, the DRI score at 1 year after injury, between the two treatment groups (standard wound dressings and negative pressure wound therapy) on an intention-to-treat basis. In addition, early functional status will also be assessed and reported at 3, 6 and 9 months. Differences between groups will be assessed, based on a normal approximation for the DRI score at 12 months postinjury and at interim occasions. Tests will be two sided and considered to provide evidence for a significant difference if p values are less than 0.05 (5% significance level).

The stratified randomisation procedure should ensure a balance in Gustilo and Anderson grade and the recruiting centre's between-test treatments. Although generally we have no reason to expect that clustering effects will be important for this study, in reality, the data will be hierarchical in nature, with patients naturally clustered into groups by the recruiting centre. Therefore, we will account for this by generalising the conventional linear (fixed effects) regression approach to a mixed effects modelling approach, where patients are naturally grouped by recruiting centres (random effects). This model will formally incorporate terms that allow for possible heterogeneity in responses for patients due to the recruiting centre, in addition to the fixed effects of the treatment groups, Gustilo and Anderson grade, and other patient characteristics that may prove to be important moderators of the treatment effect such as age and gender.

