It seems likely that some data may not be available due to voluntary withdrawal of patients, lack of completion of individual data items or general loss to follow-up. Where possible, the reasons for data ‘missingness’ will be ascertained and reported. Although missing data is not expected to be a problem for this study, the nature and pattern of the missingness will be carefully considered—including, in particular, whether data can be treated as missing completely at random. If judged appropriate, missing data will be imputed, using the multiple imputation facilities available in R (http://www.r-project.org/). The resulting imputed datasets will be analysed and reported, together with appropriate sensitivity analyses. Any imputation methods used for scores and other derived variables will be carefully considered and justified. Reasons for ineligibility, non-compliance, withdrawal or other protocol violations will be stated and any pattern observed will be summarised. More formal analysis, for example, using logistic regression with ‘protocol violation’ as a response, may also be appropriate and aid interpretation. About 1–2% of patients are expected to die during follow-up; so this is unlikely to be a serious cause of bias. However, we will conduct a secondary analysis taking account of the competing risk of death, using methods described by Varadhan *et al*.^22^

The main analyses will be conducted using specialist mixed effects modelling functions available in the software package R (http://www.r-project.org/) where DRI data will be assumed to be normally distributed, possibly after appropriate variance stabilising transformation. The primary focus will be the comparison of the two treatment groups of patients, and this will be reflected in the analysis which will be reported together with appropriate diagnostic plots that check the underlying model assumptions. Results will be presented as mean differences between the trial groups, with 95% CIs.

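### The primary 12-month model gives no role to the DRI collected at 3, 6 and 9 months, and whether missing scores are imputed is left to an undefined judgement that singles out MCAR

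*Protocol article*

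**What the plan says.** All of this comes from the protocol article. Its statistical analysis plan is promised but not shown.

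- **Primary model (Main RCT).** The comparison is of DRI one year after injury. The mixed model has recruiting centre as the random effect and treatment, Gustilo and Anderson grade and characteristics such as age and gender as fixed effects. No patient-level or repeated-measures term is described.
- **Earlier scores (Main RCT).** Their stated use is descriptive and occasion by occasion: "early functional status will also be assessed and reported at 3, 6 and 9 months". The Follow-up section confirms that DRI is collected at 3, 6, 9 and 12 months.
- **Missing data (Main RCT).** Missing data are not expected to cause difficulty, but their nature and pattern will be considered, "including, in particular, whether data can be treated as missing completely at random". Then: "If judged appropriate, missing data will be imputed, using the multiple imputation facilities available in R". Reasons for missingness will be reported, imputation methods justified, and the imputed analyses accompanied by sensitivity analyses.
- **Expected loss (Sample size).** "Allowing a margin of 10% loss during follow-up", deaths included, the target becomes 460.
- **Withdrawal (Post randomisation withdrawals/exclusions).** Under the second of three options, data gathered before withdrawal stay in the final analysis.

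**The concern.** Three features act together.

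First, MCAR is the only mechanism named, and it is a poor one to judge by. Observed data can contradict MCAR but cannot establish it, and failing to detect a departure does not justify complete cases. It is also not the assumption that either analysis needs. The adjusted 12-month model needs missingness to be unrelated to 12-month DRI given its covariates. Multiple imputation needs missing at random given the imputation variables.

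Second, the trigger for imputation is undefined, so the choice could be made after the data are seen. Patients and treating surgeons are unblinded (Blinding), and the outcome is self-reported.

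Third, patients with earlier scores but no 12-month score are foreseeable. The first three questionnaires go by post, while the 12-month one is completed at a clinic visit (Follow-up), and attendance may depend on recovery. Without imputation these patients drop out of the primary estimate. The second withdrawal option then keeps their data for the interim summaries only.

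At stake is bias in the primary contrast if loss relates to recovery differently in the two arms, when data that could reduce it have been collected.

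**Working it through.** **1. The plan's own figures.** Inputs: 8-point MCID, SD 25, 90% power, two-sided 5%, 1:1 allocation, 10% loss (Sample size, Main RCT, Randomisation).

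- Per arm: 2 × (1.960 + 1.282)² × 25² / 8² = 205.2, so 206, or 412 in total, as stated.
- Inflated: 412 / 0.90 = 457.8, so 458; the plan rounds to 460.
- Completers at 10% loss: 460 × 0.90 = 414, which gives 90.2% power.

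The sample size is sound, so the issue is bias and discretion.

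**2. A patient with DRI at 3, 6 and 9 months only.** Under the stated model there is no 12-month response and no term through which earlier scores enter, so the contribution is nil. Under imputation the patient contributes, and the earlier scores help if they are in the imputation model. The protocol fixes neither choice.

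**3. Complete-case bias.** Assumptions not in the documents: correlation ρ between 9- and 12-month DRI from 0.5 to 0.9, and log-odds of a missing 12-month score rising by b per SD of 9-month DRI. Let x be the standardised 9-month DRI. For one arm:

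bias = 25 × ρ × E(x | observed), where E(x | observed) = −(0.10 / 0.90) × E(x | missing).

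With exactly 10% missing, numerical integration gives E(x | missing) = 0.440 for b = 0.5 and 0.817 for b = 1. Hence E(x | observed) = −0.0488 and −0.0908.

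| Dependence on 9-month DRI | ρ = 0.5 | ρ = 0.9 |
|---|---|---|
| Same in both arms | 0 | 0 |
| One arm only, b = 0.5 | 25 × 0.5 × 0.0488 = 0.6 | 25 × 0.9 × 0.0488 = 1.1 |
| One arm only, b = 1 | 25 × 0.5 × 0.0908 = 1.1 | 25 × 0.9 × 0.0908 = 2.0 |

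The table shows absolute values. If worse-off patients are lost, that arm looks better than it is. Simulation with about 10% missing gave 0.6 to 1.1 and 1.2 to 2.1 points for the two one-arm rows, which agrees within simulation error. Against the MCID: 0.6/8 = 8% up to 2.1/8 = 26%.

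**4. Type I error.** The complete-case SE is 25 × √(2/207) = 2.46. Bias divided by SE runs from 0.25 to 0.83 across the one-arm rows. A nominal 5% test then rejects about 6% to 13% of the time; simulation gave 6% to 14%.

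**5. Using the 9-month DRI.** In simulations of strong (b = 1) dependence, the bias fell to about 0 (at most 0.2 points, within simulation error). This is what theory predicts, because missingness was generated from the 9-month score alone.

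**6. Precision.** Effective n per arm = 230 / [(1 − ρ²)/0.90 + ρ²], which is 212.3 at ρ = 0.5 and 225.2 at ρ = 0.9, against 207. The SE falls from 2.46 to 2.43 or 2.36, about 1% to 4%. Power rises from 90.2% to 90.9% or 92.5%.

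**The case against.** The strongest reply is that this is detail for the statistical analysis plan. The article says a detailed plan will be agreed with the DMC, and imputation triggers and variables normally sit there. That stands for the undefined trigger taken alone. It does not cover the 12-month model or the emphasis on MCAR, which the article states and a later plan would inherit.

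Four stronger readings are tempting, and the documents do not support them.

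- **That the protocol leaves the earlier DRI out of the imputation.** It names no imputation variables, so those scores may be used. They are absent only from the stated primary model.
- **That MCAR is a strict gate for imputation.** It is one named consideration, and the imputation sentence follows separately. Doubt about MCAR could well lead to imputation.
- **That expecting little trouble from missing data contradicts the 10% allowance.** The loss is budgeted for and 90.2% power remains.
- **That using earlier DRI would secure the primary result.** It removes bias only under missing at random given those scores. It does not help under not-at-random loss or for patients with no follow-up DRI.

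It is also fair to say that a 12-month model with multiple imputation is accepted practice, that telephone completion and retention efforts are planned, and that the bias figures depend on assumed differences between arms. If the arms behave alike, the bias is nil.

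**Conclusion.** The point holds as a cheap improvement. The stated primary model gives no role to three of the four follow-up DRI scores, and their only route into the primary estimate is an imputation step that may or may not be taken, with MCAR the one mechanism named.

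With about 10% missing and SD 25, the possible bias runs from nil (same mechanism in both arms) to about 2.1 points (strong dependence on 9-month DRI in one arm only), with 0.6 to 1.1 points for moderate dependence. The correlation and the missingness mechanism are assumptions; the documents supply neither, and they do not show that missingness will differ by arm. The gain in precision is small and is not the reason to change. The sample size of 460 is unaffected.

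**What to change.** Before data are seen:

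1. Replace the MCAR criterion with a stated assumption: missing at random given treatment, the model covariates and earlier DRI.
2. Give the earlier DRI a defined role in the primary 12-month estimate, by one of two routes:
   - a repeated-measures mixed model of DRI at 3, 6, 9 and 12 months, with treatment-by-time terms and patient and centre random effects, taking the 12-month treatment contrast as primary; or
   - the present 12-month model with multiple imputation mandated, done by arm, with the 3-, 6- and 9-month DRI as predictors.
3. Make the promised sensitivity analysis a delta-adjusted not-at-random analysis, with shifts allowed to differ by arm, and do it whichever route is taken.
4. State how patients with no follow-up DRI, and the 1–2% expected to die, enter the estimate.

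The cost is wording in the protocol or analysis plan and some analyst time, with the same data, software and sample size. The downside is a slightly more complex primary analysis.

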### Economic evaluation

An economic evaluation will be integrated into the trial design. The economic evaluation will be conducted from the recommended NHS and personal social services perspective.^23^ Data will be collected on the health and social service resources used in the treatment of each trial participant during the period between randomisation and 12 months postrandomisation. Trial data collection forms will record the duration of each form of hospital care, surgical procedures, adjunctive interventions, medication profiles and tests and procedures. Observational research may be required to detail additional staff and material inputs associated with clinical complications. At 3, 6, 9 and 12 months postrandomisation, trial participants will be asked to complete economic questionnaires profiling hospital (inpatient and outpatient) and community health and social care resource use, and for the purposes of sensitivity analysis, out-of-pocket expenditures and costs associated with lost productivity. Current UK unit costs will be applied to each resource item to value total resource use in each arm of the trial. *Per diem* costs for hospital care, delineated by level or intensity of care, will be calculated by the health economics researcher using data from detailed questionnaires completed by the local finance departments, giving cost data and apportioning these to different categories of patient using a ‘top-down’ methodology. The unit costs of clinical events that are unique to this trial will be derived from the hospital accounts of the trial participating centres, although primary research that uses established accounting methods may also be required. The unit costs of community health and social services will largely be derived from national sources, although some calculations from first principles using established accounting methods may also be required.^24^ Trial participants will be asked to complete the EuroQol EQ-5D^15^ and SF-12^25^
^26^ measures at 3, 6, 9 and 12 months postrandomisation. Responses to the EQ-5D and SF-12 will be converted into MAU scores using established algorithms.^16^
^17^

An incremental cost-effectiveness analysis, expressed in terms of incremental cost per QALY gained, will be performed. Results will be presented using incremental cost-effectiveness ratios (ICERs) and cost-effectiveness acceptability curves (CEACs) generated via non-parametric bootstrapping. This accommodates sampling (or stochastic) uncertainty and varying levels of willingness to pay for an additional QALY. Owing to the known limitations of within-trial economic evaluations,^26^ we will also construct a decision-analytical model to model beyond the parameters of the proposed trial the cost-effectiveness of negative pressure wound therapy in this clinical population. The model will be informed partly by data collected as part of the proposed trial, and also by data collected from other primary and secondary sources, including data sets held by the research team. Long-term costs and health consequences will be discounted to present values using discount rates recommended for health technology appraisal in the UK.^23^ A series of probabilistic sensitivity analyses will be undertaken to explore the implications of parameter uncertainty on the ICERs. Probabilistic sensitivity analyses will also explore the effects of extending the study perspective, target population, time horizon and decision context on the ICERs. In addition, CEACs will be constructed using the net benefits approach.

## Discussion

This pragmatic, multicentre trial is due to deliver results in Spring 2017. Results will be disseminated through peer-reviewed publications, including a National Institute for Health Research Health Technology Assessment monograph. Participants of the trial will receive a lay summary of the trial results.
